#### RCT secondary outcomes

We will also conduct a secondary analysis using years of CRC screening coverage over the three-year study period as the outcome. FIT must be repeated annually, and colonoscopy typically only needs to be repeated once every 10 years. Thus, patients will be assigned one year per annual FIT completed (e.g., FIT in years 1, 2, and 3 would be assigned 3 years; FIT in year 1 and 3 would be assigned 2 years) and up to 3 years for colonoscopy depending on the year received (e.g., colonoscopy in year 1 would be assigned 3 years, colonoscopy in year 3 would be assigned 1 year). Patients with a positive FIT result must complete a colonoscopy to count as covered. We will also collect patient-level data from the EHR record on appointment status, race, ethnicity, age, gender, insurance status, co-morbidities, and prior CRC screening to use as covariates or stratified analyses as appropriate.

#### Patient process and implementation measures

We will also invite patients randomized to the intervention to complete an online survey that will assess satisfaction and acceptability of digital interventions using constructs from the Technology Acceptance Model (e.g., ease of use, perceived helpfulness, and perceived usefulness) [22–25], decisional satisfaction [26, 27], and an assessment of culturally and linguistically appropriate care [28]. Details on the measures are provided in Table 1.

**Table 1 Tab1:** Implementation survey measures for clinical providers and staff and patients

Provider and staff survey	Description	Source
Acceptability	Eight items with a 5-point ordinal rating scales that measure seven constructs from the theoretical framework of acceptability including affective attitude, burden, ethicality, intervention coherence, opportunity costs, perceived effectiveness, and self-efficacy.	Theoretical Framework of Acceptability questionnaire [25]
Sustainability	Seven items that measure capacity for program sustainability, including within domains of engaged staff and leadership, engaged stakeholders, organizational readiness, workflow integration, implementation and training, monitoring and evaluation, outcomes and effectiveness	Adapted from Clinical Sustainability Assessment Tool [31]
Cultural Sensitivity	14 items with 5-point ordinal rating scale that ranged from “not at all” to “excellent” that provide a self-evaluation of knowledge (6 items), skills (6 items), and attitudes (4 items) relevant to cultural sensitivity.	Adapted from Culhane-Pera et al.’s Multicultural Assessment Questionnaire [32]

Patient survey	Description	Source
Acceptability of digital interventions	Twelve items that assess ease of use (e.g., “It was easy to use mPATH-Cloud”), trust (e.g., “I trust the information provided by mPATH-Cloud about CRC”, and overall likeability (e.g., “I would recommend mPATH-Cloud to a friend or family member”) of the digital intervention on 5-point rating scales (1 strongly disagree; 5 strongly agree)	Adapted from acceptability and ease of use surveys [22–24]
Decisional satisfaction	Six items (e.g., “The decision I made was the best decision possible for me personally”) that assess patient satisfaction with a health care decision, rated on a 5-point ordinal rating scale (1 strongly disagree; 5 strongly agree)	Satisfaction with Decision scale [26, 27]
Cultural sensitivity	Six items (e.g., “my doctor understands my background and values”) that assess perceived provider (3 items) and health system (3 item) cultural sensitivity	Bias and Cultural Competence measures [28]

#### Clinic provider and staff implementation measures

Table 2 provides an overview of the measures for provider interviews and Table 1 provides an overview of provider/staff survey measures. Our evaluation of implementation outcomes is guided by the process redesign framework (PRF) [29]. We will include measures within each domain of the PRF but will focus on those most relevant to this project. Specifically, emphasis will be placed on specific domains at different stages of the study. Early implementation interviews will focus more heavily on general processes for CRC screening and the integration and redesign of those processes for effective and efficient implementation of mPATH^®^-CRC. For provider surveys, we will also use validated surveys including Weiner et al.’s Acceptability of Intervention Measure, Feasibility of Implementation Measure, and Intervention Appropriateness Measure [30], Clinical Sustainability Assessment Tool [31], and Culhane-Pera et al.’s Multicultural Assessment Questionnaire [32].

**Table 2 Tab2:** Implementation interview constructs and measures

Constructs	Description or Guiding Questions
**Clinic Staff and Provider Early Implementation Interviews**	
***Intervention Characteristics***	
Workflows	What are the current and needed changes to processes and tasks required of interconnected stakeholders (providers, IT staff, FIT processing lab) to implement mPATH^®^-CRC
Tasks/Process Standardization	In the process design for implementation, which tasks and processes can be standardized and what are the protocols for standardization across interconnected stakeholders
***Outer Setting***	
Technological Changes	Are there changes in technology (e.g., acceptability, cost, etc.) that may impact mPATH^®^-CRC?
***Inner Setting***	
HIT/IT systems	What is the current technology infrastructure (e.g., EHR) and what is required to support integration of mPATH^®^-CRC for managing patient care, data, and communication?
Staff Resources	What is the staff time required to assist with implementation tasks such as querying patients due for screening, quality assurance of data, follow-up of abnormal FIT, etc.?
**Clinic Staff and Provider mid-term implementation interviews**	
***Implementer Characteristics***	
Skills/Competencies	What is the expertise, skills, and competencies of implementation stakeholders relevant to mPATH^®^-CRC implementation? To what extent do providers at mPATH^®^-CRC implementation sites exhibit cultural humility and linguistic sensitivity to their patients?
Roles	What are the individual and team roles/responsibilities for implementation and to what extent are there multiple/shared roles for implementation of mPATH^®^-CRC?
***Process***	
Acquiring/allocating resources	What are the major resources dedicated to implementing mPATH^®^-CRC (staff time, space, equipment)? To what extent are those resources adequate or inadequate?
Process ownership	Who is making mPATH^®^-CRC implementation decisions? How often are decisions made and how involved are decision-making processes? Is the approach top-down, bottom-up, a blend?
Decision making	Who has a major role in implementing mPATH^®^-CRC? What are their role(s) and how are they varied/different? In what ways, if any, has there been authority, accountability for these roles?
**Clinic Staff and Provider late implementation interviews**	
***Implementation***	
Penetration	To what extent have processes and tasks for implementation of mPATH^®^-CRC been integrated into the clinic’s workflows and other subsystems such as the EHR?
Replicability	To what extent is mPATH^®^-CRC perceived as replicable in other settings and clinics?
Evolvability	Does mPATH^®^-CRC require continued adaptations and refinements for sustainability? If any, what are these types of adaptations and changes?
Sustainability	To what extent are the clinic leadership, staff, and providers interested in sustaining the use of mPATH^®^-CRC? What do you think would be needed to sustain mPATH^®^-CRC?

### Analyses

#### RCT primary outcome analyses

For the RCT design, our main statistical test for the primary outcome (CRC screening completion) will be a Mantel-Haenszel chi squared test, adjusted for stratification factors (appointment status, race/ethnicity), following the intention to treat principle. If there are differences between the arms across baseline variables known to be associated with the outcome, we will use multiple logistic regression, adjusting for the variables. Specifically, due to the potential for differential response, sex will be included in all analyses as a biologic variable. One-sided tests will be used because we expect active intervention will lead to more favorable results compared to usual care. Under the intention to treat principle, our primary analysis will be a crude comparison of proportions of completed CRC screening at six months between the mPATH^®^-CRC and usual care arm using a one-sided Mantel-Haenszel chi-squared test, controlling for stratification factors (appointment status and race/ethnicity), conducted at the 0.05 significance level. As a minimal risk study using only strategies known to improve evidence-based screening, we will not convene a formal data monitoring committee.

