## Methods/Design

We will conduct a patient-level, pragmatic randomized controlled trial (RCT) to assess the impact of mPATH^®^-CRC on CRC screening rates over a three-year period. As a pragmatic trial, our goal is to determine if the intervention can improve current practice. Thus, the comparator arm patients will be assigned to usual care. Embedded within the RCT, we will use a convergent, mixed methods design for evaluation of the implementation process over the three-year implementation period. Implementation measures will also be used to understand unintended trial effects. All protocols have been reviewed and approved by the University of North Carolina at Chapel Hill and Wake Forest University institutional review boards, which granted a waiver of informed consent. Multiple data sharing, management, and security agreements were also reviewed and completed amongst UNC, FQHC, mPATH^®^-CRC, and other relevant partners. SPIRIT guidelines were used for reporting [17].

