#### Intervention arm

As shown in Fig. 1, patients selected for the intervention will be sent a text message that indicates they may qualify for a CRC screening and provides a link for further information, which directs them to the mPATH^®^-CRC interface. Patients without cell phone numbers will be mailed an invitation with the same information and a tiny URL and personal code to access the interface, although we anticipate this will be < 5% of participants. Within the mPATH^®^-CRC interface, patients will first answer a series of questions to confirm CRC screening eligibility and assess for risk factors that would change screening recommendations. If eligibility for routine CRC screening is confirmed, they will view a previously validated decision aid about CRC screening that provides information about their testing options, i.e., FIT or colonoscopy. After the video, patients are given the option to “self-order” either of those tests.

The FQHC will have its own secure mPATH^®^-CRC dashboard that displays patient requests for screening tests. The mPATH^®^-CRC system automatically emails designated staff a secure link to the dashboard when new patient screening requests occur. Notices of patients who select colonoscopy will be sent to the FQHC’s referral coordinators for further scheduling and communication. To integrate with the FQHC’s FIT processing and communication, patients who select FIT will be mailed a FIT kit using the FQHC’s usual FIT and lab vendors. Any patients who fail to engage with mPATH^®^-CRC interface within approximately 2 weeks of the initial text or mailed invitation will be mailed a FIT kit by default. The research team will have access to the mPATH^®^-CRC dashboards for implementation evaluation and will assist with prompting patient follow-up care and assistance, as appropriate.

All interface materials and communication will be offered in either English or Spanish, dependent on the patient’s language preference, including the decision aid video. Participants will also have the option to view a decision aid developed and culturally adapted in partnership with tribal communities in the state [20].

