#### RCT sample size and power

Based on our prior studies (33–37), we anticipate CRC screening rates will be between 5 and 12% in usual care and 10–35% in the mPATH^®^-CRC arm, with at least a 5–7% absolute difference between arms, conservatively. With *n* = 500 in each arm, we will have more than 80% power to detect such differences (5–7%) between the arms at 1-sided alpha level 0.05.

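### The primary test is one-sided at 0.05 solely because benefit is expected, so the chance of a false benefit claim is 5% rather than the conventional 2.5%

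*Protocol article*

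**What the plan says.** Under RCT primary outcome analyses, the protocol article gives the rule and its only reason together: "One-sided tests will be used because we expect active intervention will lead to more favorable results compared to usual care". The same paragraph specifies the comparison of completion proportions at six months "using a one-sided Mantel-Haenszel chi-squared test, controlling for stratification factors (appointment status and race/ethnicity), conducted at the 0.05 significance level".

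RCT sample size and power uses the same level. It expects screening rates "between 5 and 12% in usual care and 10–35% in the mPATH^®^-CRC arm", with an absolute difference of at least 5 to 7 points. With 500 per arm it claims more than 80% power to detect such differences "between the arms at 1-sided alpha level 0.05".

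RCT secondary analyses names a Wilcoxon rank sum test for years of screening coverage, with neither sidedness nor level. It also promises the mean, standard deviation, median and range by group.

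**The concern.** Most superiority trials expect benefit, so the expectation cannot by itself justify a one-sided test at 0.05. Dropping the other direction needs an argument that a worse result is impossible or of no interest, and the article makes neither. A one-sided test is not itself the difficulty: at 0.025 it would demand the usual strength of evidence for benefit. The difficulty is one-sided testing at 0.05, which is a two-sided 0.10 test in the direction of benefit.

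Two things are at stake. A primary result with a one-sided p-value between 0.025 and 0.05 would be declared effective here and would miss the conventional threshold. And if the general sentence governs the coverage outcome as well, no formal test would address a loss of coverage in the intervention arm.

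**Working it through.** **Inputs.** From RCT sample size and power: n = 500 per arm; usual care 5–12%; difference 5–7 points; one-sided alpha 0.05. The article does not say which difference goes with which usual-care rate, so both were varied over the stated ranges.

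**Error rate.** The critical value is 1.645 one-sided at 0.05 and 1.960 two-sided at 0.05. The chance of falsely claiming benefit is 0.05 in the first case and 0.05 / 2 = 0.025 in the second. The ratio is 2.

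**Power formula.** Two proportions with pooled variance under the null, unstratified, as an approximation to the Mantel-Haenszel test:

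power = Φ{ [d√n − z√(2p̄(1−p̄))] / √(p1(1−p1) + p2(1−p2)) }, where d = p2 − p1 and p̄ = (p1 + p2)/2.

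**The plan's own figure, at 5 v 10%.**
- d√n = 0.05 × 22.361 = 1.118
- √(2 × 0.075 × 0.925) = 0.3725
- √(0.0475 + 0.09) = 0.3708
- One-sided: (1.118 − 1.645 × 0.3725) / 0.3708 = 1.363, power 91.4%. More than 80% is reproduced.
- Two-sided: (1.118 − 1.960 × 0.3725) / 0.3708 = 1.046, power 85.2%.

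**The weakest planned case, 12 v 17%.**
- √(2 × 0.145 × 0.855) = 0.4980
- √(0.1056 + 0.1411) = 0.4967
- One-sided: (1.118 − 1.645 × 0.4980) / 0.4967 = 0.602, power 72.6%. More than 80% is not reproduced.
- Two-sided: (1.118 − 1.960 × 0.4980) / 0.4967 = 0.286, power 61.3%.

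**Across the planning range, 500 per arm.**

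| Usual care v intervention | One-sided 0.05 | Two-sided 0.05 |
|---|---|---|
| 5 v 10% | 91.4% | 85.2% |
| 7 v 12% | 85.4% | 77.0% |
| 10 v 15% | 77.3% | 66.7% |
| 12 v 17% | 72.6% | 61.3% |
| 12 v 18% | 84.5% | 75.8% |
| 5 v 12% | 99.0% | 97.9% |
| 10 v 17% | 94.6% | 90.1% |
| 12 v 19% | 92.2% | 86.5% |

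The highest usual-care rate at which a 5-point difference keeps 80% power is about 8.9% one-sided and about 6.2% two-sided. For 6 points, one-sided power stays above 80% up to 12% usual care; two-sided it does so up to about 10.2%. For 7 points both tests stay above 80% throughout. Unpooled variance gives nearly the same results (12 v 17%: 72.8% and 61.4%).

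**The case against.** The choice is prespecified, disclosed and consistent between the analysis and power sections, and the test holds its declared 5% level. The aim in Methods/Design, to see whether the intervention can improve current practice, points one way. The expectation also has support: the Background cites a trial of the iPad version with 30% v 15% completion. All of this stands, and doubling is measured only against the two-sided 0.05 convention. But earlier success in a different setting, with delivery at appointments, does not exclude a worse result here. Nor does it explain why 0.05 rather than 0.025 should be spent on the benefit side.

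Stronger readings are tempting, and the document does not support them:

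- *Every test is one-sided at 0.05.* The 0.05 level is attached only to the primary test and the power statement. The section on the Wilcoxon test is silent, and a condensed article may leave that to the full plan.
- *Default FIT displaces colonoscopy and so lowers the primary outcome.* Patients who do not engage "will be mailed a FIT kit by default", but a normal FIT counts the same as a colonoscopy in the primary outcome.
- *Such a shift must lower coverage.* It is true that "colonoscopy in year 1 would be assigned 3 years" against one year per FIT. But the outreach is repeated yearly, and FIT in all three years also earns three years. No displacement rate is given.
- *Lower coverage would be hidden.* The promised summaries by group would show it; what would be lacking is a formal test.
- *The plan contradicts itself on unintended effects.* The sentence reads "Implementation measures will also be used to understand unintended trial effects", which assigns them to the implementation evaluation and not to the trial's hypothesis test.

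**Conclusion.** The point holds for the primary test. Its sidedness rests on an expectation that does not justify it, and the chance of a false benefit claim is 5% where convention allows 2.5%. For the coverage test the point is conditional: it applies only if the general sentence is meant to extend to it.

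The one-sided level does not secure the stated power either. More than 80% for 5–7 points already fails as written for 5 points once usual care exceeds about 8.9%. So keeping the one-sided test does not rescue the claim, and restating power for a two-sided test should not conceal that case.

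The figures assume 500 analysed per arm, an unstratified approximation to the stratified test, and free pairing of the stated ranges. This is a change that should be made, not a defect that invalidates the trial.

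**What to change.** 1. Make the primary Mantel-Haenszel test two-sided at 0.05, or equivalently one-sided at 0.025.
2. State that the Wilcoxon test of coverage is two-sided.
3. Report 95% confidence intervals for the differences between arms.
4. Restate power with 500 per arm at two-sided 0.05 over the whole planning range: at least 86% for 7 points across 5–12% usual care; for 5 points, 85% at 5 v 10%, below 80% above about 6.2% usual care, and 61% at 12 v 17%.

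The cost is lower stated power: 91% to 85% at 5 v 10%, and 73% to 61% at 12 v 17%. Sample size, procedures and data collection stay as they are. Securing 80% power at 12 v 17% would need about 778 per arm two-sided, and about 613 even one-sided, so that scenario is beyond 500 per arm under either test and should be acknowledged as such.

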### Participants

#### RCT participants

We will work with the participating FQHC to develop and validate a query of their EHR to identify patients aged 45 to 73 who are average risk for CRC, overdue for CRC screening, and have had at least one clinic visit in the past 12 months. We will exclude patients with a history of CRC or adenomas, total colectomy, family risk of CRC, or diagnosis of inflammatory bowel disease. Overdue for CRC screening is defined as no stool-based (FIT, FOBT) screening within the past one year, no stool DNA test within the past three years, and no colonoscopy within the past ten years.

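### The primary test is valid but gives prior CRC screening no prespecified role; adding it as a stratifier is a small, free efficiency gain

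*Protocol article*

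**What the plan says.** Under RCT primary outcome analyses, the Protocol article names the primary comparison as screening completion at six months, tested "using a one-sided Mantel-Haenszel chi-squared test" and "controlling for stratification factors (appointment status and race/ethnicity), conducted at the 0.05 significance level". These are the two factors within which patients are randomized. The same section adds two statements about covariates. Logistic regression will be used if the arms differ on baseline variables known to predict the outcome, and sex is to be part of every analysis.

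Under RCT secondary outcomes, the list of EHR variables ends with "co-morbidities, and prior CRC screening to use as covariates or stratified analyses as appropriate". Prior screening is therefore foreseen as a covariate, but no analysis is named for it.

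Under RCT participants, being overdue includes "no stool-based (FIT, FOBT) screening within the past one year", with longer windows for stool DNA and colonoscopy. The trial can therefore enrol both patients whose annual test has lapsed and patients who were never tested.

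**The concern.** All participants are overdue, but they need not be alike. A patient who has completed a test before may well be more likely to complete another within six months than one who never has. If so, prior screening explains part of the outcome variation, and a test stratified only on appointment status and race/ethnicity leaves that part in the error.

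The text does offer a route for such variables, but it opens only after the arms have been compared at baseline, and it leads to a different analysis. It neither secures the precision in advance nor changes the deciding test. At stake is a little power, in a design that is tight over part of its anticipated range. The validity of the result is not at stake.

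**Working it through.** **Inputs from the article.** 500 per arm; one-sided alpha 0.05 (z = 1.645); usual care 5–12%; difference 5–7 points. Strata: 2 appointment groups × 4 race/ethnicity groups = 8, averaging 1000/8 = 125 patients.

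**Inputs assumed, because the article gives none.** Share ever screened 20–50%, and odds ratio 1.5 to 5 for completion in ever- versus never-screened patients. At these event rates, a completion ratio of 2 to 4 corresponds to an odds ratio of about 2.3 to 5.

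**Step 1: the stated power.** Power = Φ[(d − 1.645·√(2p̄(1−p̄)/n)) / √((p₁(1−p₁)+p₂(1−p₂))/n)], where d = p₂ − p₁ and p̄ is the mean of the two rates.

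- 12% v 17%: p̄ = 0.145; pooled SE = √(2·0.145·0.855/500) = 0.02227; unpooled SE = √((0.1056+0.1411)/500) = 0.02221; (0.05 − 0.03663)/0.02221 = 0.602; power 72.6%.
- By the same formula: 5% v 10% gives 91.4%, 12% v 19% gives 92.2%, 9% v 14% gives 79.8% and 10% v 15% gives 77.3%.

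The article's figure, "we will have more than 80% power to detect such differences (5–7%) between the arms at 1-sided alpha level 0.05", is reproduced when the ends of the ranges are paired (5 points at 5%, 7 points at 12%). For a 5-point difference, power is already just under 80% at 9% usual care.

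**Step 2: variance removed by splitting on prior screening.** Each arm's rate is split into never- and ever-screened rates that average to it, and the within-group variance is compared with the total. For 12% v 17%, 40% ever screened and odds ratio 3, the rates are 7.3% and 19.1% in usual care, 10.7% and 26.4% in intervention. The group means over arms are 0.090 and 0.2275. Within-group variance = 2(0.6·0.090·0.910 + 0.4·0.2275·0.7725) = 0.2389, against 2·0.145·0.855 = 0.2480. That is 3.7% lower.

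**Step 3: cost of the extra cells.** Randomization balances the 8 strata but not the halves of each. Splitting a balanced stratum of N in two costs about 1/N of its information, here 1/125 = 0.8%. If prior screening predicts nothing, that cost is all that remains: 0.4% of the signal-to-noise ratio 0.05/0.02227 = 2.245 is 0.009, and times the normal density at 0.602 (0.333) this is about 0.3 points of power lost.

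**Step 4: results for 12% v 17%, 40% ever screened.**

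| Odds ratio | Variance removed | Power before cell cost | Net of 0.8% |
|---|---|---|---|
| 1.5 | 0.5% | 72.8% | −0.3% |
| 2 | 1.5% | 73.2% | +0.7% |
| 3 | 3.7% | 74.1% | +2.9% |
| 5 | 7.4% | 75.5% | +6.6% |

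Where power is already ample, the gain at odds ratio 5 is at most 1.2 points (5% v 10%) and 1.8 points (12% v 19%).

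**Step 5: simulation of the actual test, 8 versus 16 strata, 40% ever screened.** At completion ratios of 2 or below there was essentially no gain, or a loss of about 0.3 points. At 10% v 15% and 12% v 17% the gain was about 1.1–1.4 points at ratio 3 and 2.0–2.3 points at ratio 4. Type I error was 4.9% with 8 strata and 5.1% with 16. The normal approximation, over 30–50% ever screened and ratios 2–4, puts the upper end at 3.2 points (12% v 17%: at most 75.8%).

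**Step 6: chance imbalance.** With 40% ever screened, the SD of the between-arm difference in that share is √(0.4·0.6·2/500) = 0.031. Times the completion gap in Step 2 (0.2275 − 0.090 = 0.1375), a 1-SD imbalance shifts the arm difference by 0.43 points. Squared, this is 0.0000182. Divided by the variance of the arm difference, 0.000496, it is 3.7%, the same 3.7% as in Step 2.

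**The case against.** The strongest reply is that nothing here is wrong. Testing on the randomization strata is sound, type I error is held, and the choice of further covariates may be left to an analysis plan that is not shown. That stands as far as validity goes. It does not fully answer the point, because the article itself lists the stratifiers of the deciding test and itself ties other predictors to an observed imbalance.

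Several stronger readings are tempting but unsupported:

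- A reader might infer that chance imbalance in prior screening biases the result. Step 6 shows that it is the same precision loss seen from another side, already counted in the test's variance.
- A reader might infer that the adjustment would rescue the power statement. It does not: 12% v 17% stays below 80% under every assumption tried.
- A reader might infer that the variable is already complete for every patient, or is returned by the selection query. The article says only that it will be collected from the EHR. A missing record may not mean never screened. Such misclassification would shrink the gain without biasing the test.
- A reader might infer that the plan ignores the variable. It names it as a possible covariate.

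It is also fair to say that a yes/no split is coarse. It groups a recently lapsed FIT with a colonoscopy more than ten years old, so completion ratios of 3 to 4 may be optimistic.

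**Conclusion.** The point holds as an optional efficiency improvement, not as an error. The deciding test leaves out a baseline variable that the article already plans to collect, and the only stated way in depends on the data. The size rests wholly on assumed prevalence and prognostic strength. The change in power is about nil, possibly −0.3 points, if completion is no more than twice as high in ever-screened patients, and a gain of about 1 to 3 points if it is three to four times as high. Neither the sample size nor the validity of the trial is affected.

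**What to change.** In RCT primary outcome analyses, state before outcomes are seen that the primary Mantel-Haenszel test is stratified by appointment status, race/ethnicity and prior CRC screening, whatever balance is observed. Define the last as any recorded CRC test before randomization, yes or no, with no record coded as no. Remove the imbalance trigger for this variable.

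Settle sex in the same sentence, since the article puts it in all analyses but not in the named primary test. Without sex there are 16 cells averaging about 62 patients. With sex as a further stratifier there are 32, averaging about 31, or roughly one or two usual-care events per cell (15.6 × 5–12% = 0.8–1.9). Mantel-Haenszel tolerates this. However, adding prior screening to strata already split by sex would cost about 2/125 = 1.6% rather than 0.8%, so the two choices should be made together.

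The cost is a sentence or two of text, with no new data, patients or contacts.
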